#### Therapists

We will train and supervise CAMHS community therapists to deliver the intervention. Therapists will contribute a full day or half a day per week, depending on the agreement with their service, to see two to four trial cases. The combined caseload across all therapists, given the study recruitment targets, will be a maximum of 24 at any one time, allowing 60 young people to be seen over a year. We will stagger the input of the therapists to accommodate the growing caseload as the study progresses.

Therapists will be trained to competence in delivery of the manualised intervention and closely supervised by the trial coordinator/supervisor. Therapy adherence will be monitored by supervisors on an ongoing basis through audio-recorded therapy sessions (for which we will request service user consent). Adherence to the manual will be checked by internal raters who are not directly involved in the care of the participant (i.e. not therapist or supervisor), using checklists of manual content incorporating general cognitive therapy skills, specific skills in working with UEDs, and appropriate tailoring to the developmental stage and presentation of each young person and family [32, 33]. An independent expert will rate 10% of internally rated sessions: we will consider 90% rated as adherent to be acceptable. For the duration of the trial, we will ensure that trained therapists do not provide care coordination for young people who are allocated to routine care. In each team, there is an early-intervention-in-psychosis liaison worker, who takes responsibility, irrespective of the trial, for ensuring that routine care meets the needs of young people presenting with psychosis.

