### Sample size

We will recruit 120 participants, randomly allocating 60 per group. From previous experience, we will allow for a conservative loss-to-follow-up of approximately 33% (85% follow-up achieved in an earlier pilot study [34]. With 45 successfully followed up in each group, we would have 80% power to detect between group differences for the smallest achieved effect sizes from previous studies of cognitive therapy with young people (0.6 SD) using a two-group *t* test with a 0.05 two-sided significance level. We will have 90% power to detect effect sizes of 0.7 SD and above. Our pilot work shows between group effect sizes of 0.6 in inpatients [32]. In practice, the power will be increased by using a mixed (random)-effects model allowing for baseline covariates including distress (rather than a simple *t* test) to gain precision in the effect estimates, but this increase is likely to be counteracted by allowing for modest between-therapist variation.

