### Statistical analysis

In accordance with Consolidated Standards of Reporting Trials (CONSORT) [94] principles, we will report all participant flow in the study. Descriptive statistics will be used to summarise assessments of feasibility and acceptability in terms of recruitment, dropout and completeness of therapy. The main efficacy analysis will be via intention-to-treat with data from all participants included in the analysis including those who do not complete therapy. When completion of the full battery of outcome measures is not possible, participants will be offered the opportunity to complete the primary outcome measure only, and as many of the main secondary outcome measures as are tolerated, in person, by telephone, or by email. Every effort will be made to follow up all participants in both arms for research assessments, and the analysis will use, where appropriate, statistical techniques for handling missing data, determined by the extent and distribution of missing data, and any identified demographic or baseline clinical predictors of missing data (age, gender, ethnicity, SDQ-E, UED severity, Severe/Other Mental Illness, borough). The primary hypothesis will be analysed using a linear mixed model allowing for the baseline measurement of SDQ-E and treatment assignment as fixed effects, with SDQ-E at 4 months as the dependent variable. Therapist effects will be modelled by including a random effect for each therapist in the therapy arm, with the control-arm participants considered as being in individual clusters of size 1. The use of a mixed (random)-effect models will allow for estimation of the intra-cluster correlation coefficient, a measure of the proportion of variance in outcome because of therapist effects, which can be used in future applications; no estimate of this is currently available. Secondary outcome measures (excluding economic outcomes) will be analysed using the same approach.

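### With controls coded as therapist clusters of size 1 and one residual variance, the promised therapist ICC is contaminated, in either direction, whenever SDQ-E variance differs between arms

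*Protocol article*

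**What the plan says.** The Statistical analysis section of the protocol article states the primary model: "The primary hypothesis will be analysed using a linear mixed model allowing for the baseline measurement of SDQ-E and treatment assignment as fixed effects". The therapist term is specified as "including a random effect for each therapist in the therapy arm". Controls are then handled as singletons, "with the control-arm participants considered as being in individual clusters of size 1". The model is meant to deliver "a measure of the proportion of variance in outcome because of therapist effects, which can be used in future applications", and the section adds that "no estimate of this is currently available". The non-economic secondary outcomes follow the same approach.

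The article does not mention a residual variance that differs by arm, and it does not say that the random effect is set to zero for the singleton controls. The Sample size section refers to therapist variation only in general terms ("this increase is likely to be counteracted by allowing for modest between-therapist variation"). No standard deviation for SDQ-E is given for either arm.

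**The concern.** Controls have no trial therapist. If each is made a cluster of one in a random-intercept model, each still receives a cluster effect with the therapists' variance. The spread of the control arm then helps to determine the therapist variance, although it holds no information about therapists. A variance difference between arms, whatever its cause, can be reported as more or less therapist clustering than exists.

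Two things are at stake. The ICC is a named product of the trial: no earlier value exists, and the Discussion plans a larger multisite study that could use it. The same variance components also set the standard error of the primary treatment effect.

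**Working it through.** **The plan's own figure.** With 45 per arm and two-sided alpha 0.05, a t test has power 80.4% at 0.6 SD and 90.7% at 0.7 SD. The stated 80% and 90% reproduce. They come from a simple t test and do not depend on how therapists are modelled.

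**Algebra.** Let s²(u) be the therapist variance and s²(e) a common residual variance.
- Therapy arm: total = s²(u) + s²(e); within-therapist variance = s²(e).
- Singleton control under the same random intercept: total = s²(u) + s²(e).

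The totals are equal by construction. Within-therapist spread pins down s²(e), so a control variance above it pushes s²(u) up, and a small control variance pulls s²(u) down. ICC = s²(u) / [s²(u) + s²(e)] moves with it.

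**Inputs for size.**
- From the article: 45 analysed per arm (Sample size). Each therapist is "to see two to four trial cases" with a combined caseload of at most 24 at a time (Therapists), so 24/4 = 6 to 24/2 = 12 therapists at full load.
- Assumed: 9 therapists x 5 = 45, balanced clusters, baseline already adjusted for, a true ICC of 0.05 unless stated, and the variances below.
- Method: REML, with a z test at 1.96 for test size and power.

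**Mean estimated ICC, true ICC 0.05.** The comparison model has the therapist effect in the therapy arm only and a residual variance per arm.

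| Therapy/control variance | Singletons, one residual variance | Comparison model |
|---|---|---|
| 1.3/0.7 | 0.054 | 0.073–0.075 |
| 1.1/0.9 | 0.067 | 0.073–0.075 |
| 1/1 | 0.078 | 0.073–0.075 |
| 0.9/1.1 | 0.100 | 0.073–0.075 |
| 0.8/1.2 | 0.142 | 0.073–0.075 |
| 0.7/1.3 | 0.213 | 0.073–0.075 |

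A check with 20,000 simulated trials per setting reproduces each singleton value to within 0.003. The comparison model averages above 0.05 because estimates cannot fall below zero, so 0.073–0.075 is the fair benchmark.

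**Not only sampling noise.** With expected mean squares in place of simulated ones (true ICC 0.05), the singleton model gives 0.085 at a control/therapy variance ratio of 1.5 and 0.220 at 2. The comparison model stays at 0.050.

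**Other layouts, true ICC 0.** Moving the ratio from 1 to 2 raises the mean singleton ICC from 0.047 to 0.183 (9 x 5), 0.044 to 0.237 (6 x 7) and 0.050 to 0.159 (12 x 4).

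**Alternative reading.** Suppose the effect acts only in the therapy arm but one residual variance is kept. Residual variances are then forced equal and the bias reverses: with true ICC 0.05, the mean ICC is 0.124 at ratio 0.5, 0.064 at ratio 1 and 0.018 at ratio 2.

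**Treatment effect, singleton model.**
- 0.7/1.3: standard error about 17% too large, test size about 4%, power at a difference of 0.6 about 66% against 77% under the comparison model.
- 1.3/0.7 with true ICC 0.10: standard error up to about 6% too small, size 6.9% against 5.9%.
- Equal variances: the two methods agree.

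**Meaning for a later trial.** For an assumed 20 cases per therapist, the therapy-arm design effect is 1 + 19 x 0.05 = 1.95 at the true ICC, 1 + 19 x 0.073 = 2.39 at the comparison model's mean, and 1 + 19 x 0.213 = 5.05 at the singleton mean under 0.7/1.3.

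**The case against.** The equality constraint needs a common residual variance, which the article does not state in words. Residual structure is often left to the SAP, and singleton coding with separate residual variances would not force equality. The wording can also be read as confining the therapist effect to the therapy arm, with singletons as a data-coding device. This stands as a limit on the claim. It does not remove it: the singleton coding is stated, nothing in the text lifts the default single residual variance, and confining the effect to the therapy arm without lifting it only reverses the bias.

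A reader might infer that the plan's ICC will be inflated, for example because therapy moves scores towards the floor. The documents do not support that. They give no variances, and varied response to therapy could make the therapy arm the more variable one. When it is, the singleton ICC is biased downward and can even have the smaller error (root mean squared error 0.087 against 0.097 at ratio 0.8, and 0.068 against 0.097 at 0.5).

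The ICC will also be imprecise under any model. The comparison model's sampling SD is about 0.09, so for ratios of about 0.8 to 1.25 the difference between methods (0.03 or less) lies well inside the noise. That is a reason to report an interval. It does not justify letting the control arm inform the therapist variance.

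Finally, a reader might infer a general false-positive problem in the primary test. The figures do not show one: the test is conservative when controls are the more variable, and only slightly liberal in the reverse case.

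**Conclusion.** The point holds in conditional form. As written, and fitted with a single residual variance, the model lets an arm difference in SDQ-E variance distort the ICC that the article promises for later use. Under the assumed layout and a true ICC of 0.05, the mean estimate ranges from 0.054 to 0.213 across the variances examined, against a stable 0.073–0.075. Distortion is slight near equal variances and large only when controls are clearly the more variable. The effect on the primary test is secondary: mainly lost power in that same setting, and a mildly small standard error in the opposite one. The stated power figures are unaffected. The sizes rest on assumed variances, number of therapists and true ICC; the algebra does not. The plan does model therapist clustering, and the correction is a cheap improvement to how it does so.

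**What to change.** Replace the singleton sentence with a partially nested specification: the therapist random effect multiplied by the therapy-arm indicator (zero for controls), a separate residual variance in each arm, and fitting by REML. Report the ICC from the therapy arm, s²(u) / [s²(u) + s²(e, therapy)], with its confidence interval. Apply the same form to the secondary outcomes analysed this way. The small-sample degrees-of-freedom method can be left to the SAP.

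The cost is one sentence and one extra variance parameter, with no change to design, data or estimand. With equal variances, test size, power and mean ICC hardly change. The ICC can be somewhat noisier than under singleton coding if the therapy arm is the more variable. It is also slightly noisier at equal variances than under a therapy-arm-only effect with one residual variance.

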**Methods:**

The CUES+ study is a randomised controlled trial comparing CBT-UED plus routine care to routine care alone. CBT-UED comprises up to 16 sessions, including up to 12 individual and up to four family support meetings, each lasting around 45–60 min, delivered weekly. The primary outcome is emotional distress. Secondary outcomes are change in UEDs, risk events (self-harm, attendance at emergency services, other adverse events) and health economic outcomes. Participants will be randomised in a 1:1 ratio after baseline assessment. Randomisation will be stratified by borough and by severity of mental health presentation: ‘severe’ (an identified psychotic or bipolar disorder) or any ‘other’ condition. Outcomes will be assessed by a trained assessor blind to treatment condition at 0, 16 and 24 weeks. Recruitment began in February, 2015 and is ongoing until the end of March, 2017.

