### Measures

#### Outcomes and timeline

Following informed consent from each participant, all outcomes will be assessed by a trained study researcher. Demographic/clinical characteristics (age, gender, ethnicity, parent-reported developmental delays, family circumstances, diagnoses), brief cognitive functioning (word reading, working memory and general intelligence) and history of adverse life events and bullying will be assessed at baseline [45–50]. Outcomes will be assessed at baseline (0 weeks) then at 16 weeks and 24 weeks post randomisation, irrespective of treatment duration. Assessments will not be completed more than 2 weeks after the planned assessment time point. Outcomes and all measures are listed in Table 1 and will be completed according to the schedule in Fig. 2.

**Table 1 Tab1:** Coping with Unusual ExperienceS for 12–18 year olds (CUES+): list of measures

Measure	Completed	
	By	At
Primary outcome		
1. Strengths and Difficulties Questionnaire-Emotional Problems (SDQ-E) [41, 42]	1	0,1
Main secondary outcomes		
2. Unusual Experiences Questionnaire – severity score (UEQ) [10, 14, 39]	1	0,1
3. Self-harm (Development and Wellbeing Scales, DAWBA) [45]	1	0,1
4. Child Clinical Service Receipt Inventory (CSRI) [51]	2,3	− 1,2
5. EuroQol Health Questionnaire, youth (EQ5D-Y) [52–54]	1,2	0,2
Other secondary child outcomes		
6. Strengths and Difficulties Questionnaire (SDQ) [41, 42]	1,2	0,1,2
7. Unusual Experiences Questionnaire (UEQ) [10, 14, 39]	1,2	0,1,2
8. Child Global Assessment Scale (C-GAS) [86]	3	0,1,2
9. Health of the Nation Outcome Scales for Children and Adolescents (HoNOSCA) [87, 88]	3	0,1,2
10. Revised Child Anxiety and Depression Scales (RCADS) [55]	1,2	0,1,2
11. Elevated Mood Scales [56–58]	1,2	0,1,2
12. Me and My School, behavioural problems (M&MS) [59]	1,2	0,1,2
13. Difficulties in Emotion Regulation Scale (DERS) [60]	1	0,1,2
14. Adolescent Dissociative Experiences Scale (A-DES) [61]	1	0,1,2
15. Child Revised Impact of Events Scale (CRIES-13) [62]	1	0,1,2
16. Eating disorder screen (DAWBA) [45]	1	0,1,2
17. Maudsley Addictions Profile (MAP) [63]	1	0,1,2
18. Time budget of activities and peer relationships [64–66]	1	0,1,2
19. Beliefs about problems (BAP) [69–72]	1	0,1,2
20. Brief Core Schema Scale [27, 68]	1	0,1,2
21. Jumping to conclusions [26, 73]	1	0,1,2
Secondary parent outcomes		
22. Five Minute Speech Sample (FMSS) [74]	2	0,1
23. Brief Illness Perception Questionnaire (BIPQ) [36, 69]	2	0,1

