#### Secondary outcomes

Secondary outcomes will be child-reported UED severity at 16 weeks, assessed using the self-report UEQ [10, 14, 39]. Self-reported self-harm [45] and adverse events including attendance at accident and emergency services, and economic costs, including quality-adjusted life years (QALYs) [51–54] will also be assessed.

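### The SDQ-E linear mixed model is extended to self-harm, emergency attendances and adverse events, whose distributions it does not fit; the cost is in interpretation and a little power, not in error rate

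*Protocol article*

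**What the plan says.** The Statistical analysis section of the protocol article fixes the primary model: "The primary hypothesis will be analysed using a linear mixed model allowing for the baseline measurement of SDQ-E and treatment assignment as fixed effects", with the 4-month SDQ-E as dependent variable. It adds a clustering term: "Therapist effects will be modelled by including a random effect for each therapist in the therapy arm", with each control treated as a cluster of one. The intra-cluster correlation to be estimated is described as "a measure of the proportion of variance in outcome because of therapist effects". The section then closes with the rule at issue: "Secondary outcome measures (excluding economic outcomes) will be analysed using the same approach".

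The outcomes under that rule are listed elsewhere. The abstract says "Secondary outcomes are change in UEDs, risk events (self-harm, attendance at emergency services, other adverse events) and health economic outcomes". The Secondary outcomes section names self-reported self-harm and "adverse events including attendance at accident and emergency services". Table 1 places self-harm among the main secondary outcomes, child-reported at baseline and 16 weeks. The safety monitoring section says that adverse events are logged as reported and checked against the medical record. The look-back is six months at baseline, then the interval since the previous assessment at 16 and 24 weeks.

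No logistic, Poisson, negative binomial or other generalised model appears in the article. Skewness is addressed only for costs, in the Bootstrap analysis section.

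**The concern.** The rule makes one exception, for economic outcomes. Read with the outcome lists, it sends event outcomes to a model built for a roughly continuous score with constant residual variance. For occurrences and counts this raises four problems:

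- The variance depends on the mean, so constant variance cannot hold if the arms differ.
- Fitted risks or rates can be negative when events are rare.
- A therapist correlation defined as a share of variance changes with how common the event is, which weakens its stated use in planning future studies.
- The model has no term for length of observation, although the windows differ between time points.

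These are the trial's risk outcomes, so their estimates should be readable as risks or rates, and the model should be settled before the data are seen.

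**Working it through.** **The plan's own figure.** The article gives no event rate and no power for an event outcome. Its only power statement concerns the primary outcome: 45 per arm, two-sided 5%. By normal approximation, power = Φ(d√(n/2) − 1.96).
- d = 0.6: 0.6 × √22.5 = 2.846, and Φ(0.886) = 81.2% (80.4% by exact t), against 80% stated.
- d = 0.7: 3.320, and Φ(1.360) = 91.3% (90.7% by exact t), against 90% stated.

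Both reproduce. The present point does not depend on them.

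**Variance and mean.** For a yes/no outcome the within-arm SD is √(p(1−p)). The rates are assumed.

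| Rates | SDs | Power at 45 per arm |
|---|---|---|
| 30% v 15% | 0.46 v 0.36 | about 40% |
| 20% v 10% | 0.40 v 0.30 | about 26% |
| 10% v 5% | 0.30 v 0.22 | about 14% |

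The variances differ. With equal arms, however, the pooled standard error of an unadjusted difference equals the unpooled one: √(2 × (s₁² + s₂²)/2 ÷ n) = √((s₁² + s₂²)/n). At 30% v 15% both are √((0.21 + 0.1275)/45) = 0.087. This is why the misfit does little damage to the test under 1:1 allocation.

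**Therapist variance share.** Suppose a small therapist effect with SD σ on the logit scale. The between-therapist variance of the risk is about {p(1−p)}²σ² and the total variance about p(1−p), so the share is about p(1−p)σ². That is 0.21σ² at a 30% rate and 0.0475σ² at 5%. The same therapist variation gives shares that differ by a factor of 0.21/0.0475 = 4.4.

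**Observation windows.** Six months is about 26 weeks. The 16-week window is shorter by a factor of 26/16 = 1.6, and the window from 16 to 24 weeks by 26/8 = 3.25. Assessments may also run up to 2 weeks late. A constant difference in window is absorbed by the baseline coefficient. Differences between participants are not, and a raw change from baseline would not compare like with like.

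**Simulation under no effect** (45 per arm, 3,000 runs per scenario, baseline-adjusted linear fit, no therapist variance):
- Type I error was 3.6% to 5.4% across all scenarios.
- Yes/no outcome: a negative fitted risk occurred in about 40% of runs when the typical participant's risk was 5%, in 7% at 10%, and in almost none at 20% or above.
- Counts: a negative fitted count occurred in about 22% of runs at a mean of 0.1, 3% at 0.3 and 7% at 1.0.

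**Simulation with an effect** (40 per arm, assumed rates, no therapist variance):
- Counts with strong over-dispersion (variance μ + 2μ²). Control mean 0.5, rate ratio 0.3: power 54–56% linear v 60–62% negative binomial. Control mean 1.0, ratio 0.4: 51% v 55–56%. The linear interval for the therapy-arm mean went below zero in about 86% and 52–53% of trials.
- The same two scenarios with milder over-dispersion (variance μ + 0.5μ²): 72% v 74% and 79% v 80%, with Monte Carlo error about 1 point.
- The negative binomial test's type I error was about 0.3 to 1.4 points above the linear test's, so part of these gaps is not real power.
- Yes/no outcome, linear v logistic: 24.9% v 24.9% (20% v 10%) and 34.3% v 35.3% (15% v 5%). Negative fitted risks occurred in 8–25% and 29–51% of trials, depending on the assumed baseline covariate.

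**Sparse arms.** At a 5% risk with 40 per arm, the chance of no events in that arm is 0.95⁴⁰ = 13%. Ordinary maximum likelihood then gives no finite odds ratio, so logistic regression alone is not a complete remedy.

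**The case against.** The strongest reply is about scope. The same approach could mean the framework (intention to treat, baseline adjustment, a therapist random effect), with the link function left to an analysis plan. The rule speaks of outcome measures, and Table 1 has no row for adverse events or emergency attendance. The service-use inventory, which would capture attendances, serves the economic analysis and is excepted. Adverse events have their own monitoring section. The self-harm response scale is stated nowhere.

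Part of this stands. That self-harm is yes/no is an inference, and attendances costed through the inventory fall outside the rule. But the only model named is linear, the therapist correlation is defined as a variance share, and the abstract lists the risk events as secondary outcomes apart from the economic ones. This is therefore a stated rule that fits poorly, not a detail left open.

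The second reply is about harm, and most of it stands. A reader might infer that the treatment estimates would have impossible confidence limits. They would not: the values below zero are fitted levels or arm means, and a difference in risk or rate may properly be negative. A linear model on a yes/no outcome estimates a risk difference, which is a useful quantity. A reader might also infer inflated false positives or a serious loss of power; the simulations show neither. Nor is the therapist variance meaningless. It can be computed for 0/1 data, but it does not carry over to a different event rate.

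**Conclusion.** The point holds as a misfit between a stated rule and some of the outcomes it covers. It is best settled for adverse events and emergency attendance recorded as such, which are logged occurrences or counts, and probable for self-harm. The consequences are awkward fitted values for rare events, a therapist correlation tied to the event rate, no allowance for observation time, and a power loss of about 2 to 6 points for over-dispersed counts. For yes/no outcomes the loss is negligible. Type I error stays near 5%, and the primary SDQ-E analysis is unaffected.

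All event rates and dispersions here are assumptions, because the documents give none, and no simulation included therapist variation. The power of these comparisons is low mainly because events are few in a trial of this size; changing the model will not alter that much.

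**What to change.** Limit the closing rule of the Statistical analysis section to continuous scores, and add a sentence for the rest:

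- **Yes/no outcomes** (self-harm if so scored, any emergency attendance): logistic regression with arm and the baseline value, reporting an odds ratio and a risk difference. Use a penalised or exact method if an arm has few or no events.
- **Event counts:** negative binomial regression, or Poisson with robust errors, with log observation time as offset and the baseline count expressed as a rate. Report a rate ratio.
- **Therapist clustering:** keep the random effect where it can be estimated; otherwise use cluster-robust errors.

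State the self-harm response scale, and say whether adverse events are to be modelled or only tabulated. The cost is a sentence or two and slightly more analysis work, with no change to data collection. The generalised models may fail to converge when events are very sparse, so the fallback should be named in advance.
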